## Abstract

**Background:**

To impact on the obesity epidemic, interventions that prevent weight gain across populations are urgently needed. However, even the most efficacious interventions will have little impact on obesity prevention unless they are successfully implemented in diverse populations and settings. Implementation research takes isolated efficacy studies into practice and policy and is particularly important in obesity prevention where there is an urgent need to accelerate the evidence to practice cycle. Despite the recognised need, few obesity prevention interventions have been implemented in real life settings and to our knowledge rarely target rural communities.

**Methods:**

Here we describe the rationale, design and implementation of a Healthy Lifestyle Program for women living in small rural communities (HeLP-her Rural). The primary goal of HeLP-her Rural is to prevent weight gain using a low intensity, self-management intervention. Six hundred women from 42 small rural communities in Australia will be randomised as clusters (n-21 control towns and n = 21 intervention towns). A pragmatic randomised controlled trial methodology will test efficacy and a comprehensive mixed methods community evaluation and cost analysis will inform effectiveness and implementation of this novel prevention program.

**Discussion:**

Implementing population interventions to prevent obesity is complex, costly and challenging. To address these barriers, evidence based interventions need to move beyond isolated efficacy trials and report outcomes related to effectiveness and implementation. Large pragmatic trials provide an opportunity to inform both effectiveness and implementation leading to potential for greater impact at the population level. Pragmatic trials should incorporate both effectiveness and implementation outcomes and a multidimensional methodology to inform scale-up to population level. The learnings from this trial will impact on the design and implementation of population obesity prevention strategies nationally and internationally.

**Trial registration:**

ANZ clinical trial registry ACTRN12612000115831. Date of registration 24/01/2012

## Background

Longitudinal data indicates mean body mass index (BMI) is increasing across all population groups. In Australia, approximately one-fifth of those who are normal weight or overweight progress to a higher weight category within 5 years [1,2]. For most people weight gain increases gradually over several decades, and is estimated to be on average 600-800 g per year [3,4]. Weight gain, even in those who are a healthy weight, is associated with an increased risk of chronic disease [5]. This supports the need for interventions to prevent weight gain in those who are currently within the healthy weight range, as well as those who are overweight or obese. Population subgroups at higher risk for rapid weight gain include young women [3] particularly those living in rural communities [6,7]. Despite the direct links between weight gain and increased risk of obesity related diseases, few interventions have specifically targeted the prevention of weight gain or women living in rural communities [6,8,9].

Prevention of weight gain is feasible, requiring only minor adjustments to lifestyle behaviours [4,10]. Our team was one of the first to demonstrate prevention of weight gain in a clustered randomised controlled trial (RCT) of 250 women with a mean age 39 years. Compared to standard health information alone, the Healthy Lifestyle Program (HeLP-her) a low intensity, self-management intervention, significantly reduced weight gain over one year in an urban population of women [4]. Following the success of HeLP-her trial in an urban population we now seek to expand the evidence for this program to include outcomes relevant to effectiveness and implementation.

A gap in research that translates evidence-based interventions from isolated efficacy trials toward broad effective population strategies is evident [11,12]. Implementation research seeks to address this gap by generating an understanding of how interventions work within real world conditions [11]. The hybrid effectiveness-implementation model retains essential features of efficacy trials (randomisation and control groups) while addressing issues important in implementation (reach, diversity of settings, satisfaction and cost) [13]. Applying this effectiveness–implementation model to obesity prevention in the community will answer important questions related to successful implementation and expedite the successful implementation of interventions into practice.

The aim of the HeLP-her Rural study is to evaluate the efficacy, effectiveness, impact and cost of implementing the HeLP-her program in small rural communities in Australia. The hybrid effectiveness–implementation design features a cluster RCT, a mixed methods community evaluation and an economic analysis to inform scale-up into diverse populations and add to current knowledge on implementing prevention interventions in general.

## Methods

### Study design

Help-her Rural is a community based, cluster RCT design. The RCT involves an active intervention phase (year 1) and an observational phase (year 2) concurrent with a comprehensive community evaluation (participants and stakeholders) and economic evaluation. The primary aim of this trial is to compare the effect of a low intensity intervention (HeLP-her Rural), with an information only control on weight gain in reproductive aged women living in small rural communities in Australia. The secondary aims are to improve health behaviours including diet quality and regular participation in physical activity; to assess the impact of HeLP-her Rural on participant engagement, health behaviour, attitudes and knowledge; to assess stakeholder experiences; and assess the cost-effectiveness of the program. Phase 1 includes a one-year, low intensity intervention using face-to-face, telephone and text messaging. Phase 2 is an observation year with no active intervention for either intervention or control groups. The study will be conducted in accordance with the Consolidated Standards of Reporting Trials (CONSORT) guidelines.

The Monash Health Human Research and Ethics Committee has approved the study, project No.12034B.

### Selecting communities

Victoria is a southern State of Australia with 34 Shires of defined geographical boundaries. Population statistics and socioeconomic data are readily available for each. Twelve of these Shires will be excluded from recruiting because of potential confounding related to their participation in a Government funded preventative health campaign. Within the remaining 22 Shires, all small rural towns with populations of between 1500–10,000 persons, located within a radius of between 100 km and 400 km from Melbourne Central Business District (CBD), will be eligible for randomisation. Town selection criteria is based on size and distance from the CBD as these factors are likely to impact on availability and access to health and community services readily available in larger regional towns. Based on these criteria, 44 towns will be eligible for randomisation.

### Sample size calculations

In the calculation of sample sizes for the primary outcome (weight change over 12 months) adjustments will be made for the cluster design. The variance inflation factor (VIF) used to achieve this is determined from the average cluster size and the Intra-Cluster Correlation (ICC). We have powered the trial to detect a difference of 1.0 kg in weight between groups at 12 months based on our previous trial [4] and estimated population weight gain [3]. Assuming a significance level of 90% for a two-sided test, 196 women per group will be required to detect the absolute difference in weight with 80% power. The actual ICC calculated in the previous HeLP-her was −0.02 using Generalised Estimating Equations (GEE) [14], and despite the negative value is assumed to be equivalent to zero. However, we are assuming some clustering in this setting although small, and as there is little published data on which to base an estimate in rural community groups, we have assumed an ICC =0.02, cluster size m = 15, and a VIF 1.28 (1 + (m-1)*0.02)*195). Therefore, 250 women per group will be required and allowing for 20% attrition in participants over 12 months we plan to recruit 600 women in 40 clusters of 15 women. Because of the complexity and cost of the RCT we plan to oversample by 2 towns and randomise 42 towns using computer generated numbers, thereby allowing for any inadvertent recruiting issues.

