### Economic evaluation

An incremental cost-effectiveness analysis will determine whether the HeLP-her Rural intervention represents “value-for-money” measured against the control intervention. Both a trial-based evaluation and a modelled lifetime evaluation will be conducted from a ‘Government healthcare as 3rd party payer’ perspective.

The *Trial-Based Evaluation* will analyse costs and outcomes observed during the active intervention. Detailed pathway analysis will be used to specify all activities undertaken as part of the intervention in order to measure costs of associated resource use. Costs will include “intervention costs” (e.g. Groups, facilitation, website maintenance, text messaging). Unit costs will be drawn from best available sources for the 2012 reference year. Outcomes as observed in the RCT will be combined with the cost data to report results expressed as the ‘the $ cost per kilogram gain prevented’.

The *Modelled Economic Evaluation* will build on the trial-based evaluation by extrapolating costs and outcomes over the lifetime of the trial participants. A Markov model will be developed to estimate the lifetime costs and quality-adjusted life years (QALYs) of patients. The analysis will assume that there are no further intervention costs after the one-year active intervention. Assumptions regarding the maintenance of the intervention effect (weight gain prevention for the intervention group) will be based on sustainability of effect observed during the post-trial observation period (data collected at 2 years) combined with published literature regarding the long-term sustainability of behaviour change interventions. QALYs will be estimated based on body mass index-specific quality of life weights and mortality rates. The cost side of the analysis will be expanded to include cost “offsets” (i.e. the costs to treat overweight/obesity-related morbidity and complications). The incremental cost-effectiveness ratio will be reported as the ‘$ cost per QALY saved’ and compared with the commonly used benchmark of ‘value-for-money’ in Australia (e.g. $50,000 per QALY saved). Standard discounting will be applied to both costs and outcomes and simulation-modelling techniques will be utilised to calculate 95% uncertainty intervals. Supplementary modelling will extrapolate results for all women in the target group at the national level.

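### The type I error of the primary test is given as a 90% significance level, with no SD to show what was meant; if two-sided 10% was used, power at 5% is about 70%, not 80%

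*Protocol article*

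**What the plan says.** The Sample size calculations section of the protocol article sets the target: "We have powered the trial to detect a difference of 1.0 kg in weight between groups at 12 months". It cites the group's previous trial and estimated population weight gain as the basis. It then states the error rate and the result: "Assuming a significance level of 90% for a two-sided test, 196 women per group will be required", the purpose being "to detect the absolute difference in weight with 80% power". The clustering step follows, with "ICC =0.02, cluster size m = 15, and a VIF 1.28 (1 + (m-1)*0.02)*195", leading to 250 women per group, a 20% attrition allowance, and 600 women in 40 clusters of 15.

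The article states no SD or variance of weight change. It names no other significance level, and no confidence level for the primary comparison. The only interval level in the article is in the Economic evaluation section, for the modelled lifetime analysis: "simulation-modelling techniques will be utilised to calculate 95% uncertainty intervals".

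**The concern.** A significance level is the probability of rejecting a true null hypothesis, so 90% cannot be meant literally. A test with alpha 0.90 rejects 90% of the time when there is no difference, so its power could not be as low as 80%. The phrase must stand for something else, and there are two natural candidates: 90% confidence, which is two-sided alpha 10%, or a slip for 95% confidence, which is two-sided alpha 5%.

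These describe different trials. Under the first, a primary test run at 10% has twice the conventional false-positive rate, and a test run at 5% has less power than stated. Under the second, the design is what it says it is and only one number is mistyped. Because the SD is absent, a reader cannot work back from 196 to find out which applies. The alpha concerns weight change over 12 months, the outcome on which the trial is sized, so the ambiguity reaches the main conclusion.

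**Working it through.** **Inputs from the Sample size calculations section.** Difference d = 1.0 kg; power 80%; two-sided test; n = 196 per group before clustering; ICC 0.02; cluster size 15. The SD is not given.

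**Formula.** For two equal groups and a normal approximation, n = 2 (z_α + z_β)² SD² / d², where z_α is the two-sided critical value and z_β = 0.842 for 80% power. Since 196 cannot be reproduced without an SD, solve for the SD instead: SD = d × √(n/2) / (z_α + z_β), with √(196/2) = 9.90.

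**Reading A, two-sided alpha 10%.**
- z_α = 1.645, sum = 2.487, squared = 6.18.
- Implied SD = 9.90 / 2.487 = 3.98 kg.
- Check with a round SD of 4.0: n = 198.

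**Reading B, two-sided alpha 5%.**
- z_α = 1.960, sum = 2.802, squared = 7.85.
- Implied SD = 9.90 / 2.802 = 3.53 kg.
- Check with a round SD of 3.5: n = 193.

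Both round values come within 3 of 196 and neither gives it exactly, so the figure itself does not favour either reading. Using 195, which appears in the article's clustering expression, shifts the implied SDs only to 3.97 and 3.53 kg.

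**Power at two-sided 5%.**
- Reading A: d / (SD × √(2/196)) = 2.487, so power = Φ(2.487 − 1.960) = Φ(0.527) = 0.70. This does not depend on the SD once 80% power at 10% is accepted.
- Reading B: 80%, as stated. A test at 10% would then have power Φ(2.802 − 1.645) = Φ(1.157) = 0.876.

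**Difference detectable with 80% power at 5% under Reading A.** 2.80 × 3.98 × √(2/196) = 1.13 kg, against the planned 1.0 kg.

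**Size needed for 80% power at 5% under Reading A.** n = 2 × 7.85 × 3.98² = 249 per group before clustering; 249 × 1.28 = 319 after it, against the stated 250.

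**Clustering step.** VIF = 1 + (15 − 1) × 0.02 = 1.28. Then 195 × 1.28 = 249.6 and 196 × 1.28 = 250.9, so the stated 250 reproduces.

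**Planned enrolment.** Of 300 women per group, 240 remain after 20% attrition. Spread over 20 towns that is 12 per town, so VIF = 1 + 11 × 0.02 = 1.22 and the effective number is 240 / 1.22 = 196.7. Power at 5% is then 70% under Reading A and 80% under Reading B, so the figures above also describe the planned enrolment.

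**The case against.** A reader might infer that the stated power is simply wrong: that 80% holds only at 10% and the trial really has 70%. The documents do not support that. The 70% follows from assuming that 196 was calculated at 10%; it is not separate evidence of a shortfall. A 5% test with an SD of 3.53 kg fits the same 196.

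A reader might also see a contradiction with the 95% intervals in the Economic evaluation section. There is none. Those are simulation intervals from a lifetime cost-effectiveness model and do not fix the level of the primary test.

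The missing SD would be weak as a point of its own. This is a condensed article that refers to the previous trial for its planning basis, and a fuller document may hold the figure. It counts here only because it would settle the meaning of the alpha.

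Finally, a two-sided 10% test is unconventional but not invalid, and no arithmetic step in the section is shown to be wrong. All of this stands and limits the claim. It does not remove the point. The test level is not left to another document: it is stated here, in a form that cannot be right, and nothing else in the article corrects it.

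**Conclusion.** The type I error rate for the primary outcome is misstated, and the article does not contain what is needed to correct it. Power for 1.0 kg at two-sided 5% is about 70% if 196 was calculated at two-sided 10% (implied SD 3.98 kg, detectable difference 1.13 kg), and 80% if it was calculated at 5% (implied SD 3.53 kg). The range is therefore 70% to 80%, and the document gives no ground for choosing within it.

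These figures rest on a normal approximation, equal groups, the article's own ICC of 0.02, and 80% power having been correctly computed at whichever alpha was used. The point is certain as to the wording and conditional as to the loss of power. It should be corrected because the sample size and the decision rule for the primary outcome both depend on this number.

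**What to change.** Replace the phrase with the two-sided alpha at which 196 was calculated, state the alpha at which the primary test will be run, and give the SD of 12-month weight change that was used. Writing in 5% without checking would not be safe: if 196 came from 10%, that edit would make the stated 80% power wrong.

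- If the calculation and the test both use 5%, correct the number and leave the power at 80%.
- If the calculation used 10% but the test will use 5%, restate the power as about 70% for 1.0 kg at the planned size.
- If the test will use 10%, say so plainly and plan to report the primary result with a 90% interval.

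The cost is a change of wording and possibly a less favourable stated power. Enrolment does not change. The limit of this fix is that, in the second case, it discloses the lower power and does not restore it; 80% at 5% would need about 319 women per group after clustering, as calculated above, in place of 250.

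### The sample size steps do not fit together: 600 recruits with 20% attrition leave 240 women per arm, not the stated 250, although the planned size can be justified

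*Protocol article*

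**What the plan says.** The Sample size calculations section of the protocol article builds the target in four steps.

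- Before any allowance for clustering, "196 women per group will be required" for a 1.0 kg difference at 12 months with 80% power.
- For clustering, "we have assumed an ICC =0.02, cluster size m = 15, and a VIF 1.28 (1 + (m-1)*0.02)*195".
- For attrition, "250 women per group will be required and allowing for 20% attrition in participants over 12 months we plan to recruit 600 women", to be found in 40 clusters of 15.
- As a reserve against recruiting problems, "we plan to oversample by 2 towns and randomise 42 towns using computer generated numbers".

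The Methods paragraph of the abstract gives the total as "Six hundred women from 42 small rural communities in Australia will be randomised as clusters", with 21 towns per arm. The sections on the intervention and the control group describe groups of approximately 15 women.

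**The concern.** The section states a requirement (250 per group), a loss (20%) and a recruitment target (600), and the three cannot all hold. A 20% allowance has to be divided out, because the loss applies to the women recruited. Here it was added on top of the women required, which understates the recruits needed for a given number of completers.

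This is the sample size justification for the primary outcome, and the 600 is repeated in the abstract. A reader who checks it finds that the stated size misses the stated requirement. The reader also cannot tell whether recruitment should stop at 600 or fill 42 towns to 15 each, which is 630. On the plan's own 250, that choice decides whether the requirement is met.

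**Working it through.** **Inputs, all from Sample size calculations:** 196 per group unadjusted (195 in the VIF expression); intra-cluster correlation (ICC) 0.02; m = 15 per town; 20% attrition; 600 recruits in 40 towns; 42 towns randomised; difference 1.0 kg; power 80%. The section gives no SD.

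**1. Reproducing the plan's figures**
- VIF = 1 + (15 − 1) × 0.02 = 1.28.
- 195 × 1.28 = 249.6 and 196 × 1.28 = 250.9, so the stated 250 reproduces.
- 250 × 1.2 = 300 per arm, 600 in total. This is the stated target.
- 250 / 0.8 = 312.5, so 313 per arm and 626 in total. This is not the stated target.

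The 600 therefore came from multiplying by 1.2.

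**2. What 600 delivers**
- 300 × 0.8 = 240 completers per arm, 10 (4%) below 250.
- Attrition at which 300 recruits still leave 250: 1 − 250/300 = 16.7%.

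**3. Power at the plan's VIF**

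Assumption: the SD is the one that makes 196 per group give 80% power. The section words its significance level as 90%, two-sided. Read as alpha 0.10, the SD is 1.0 / [(1.645 + 0.842) × √(2/196)] = 3.98 kg. At alpha 0.05 it is 3.53 kg.

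Effective n per arm = completers / VIF, and power = Φ(1.0 / (SD × √(2/n)) − z), with z = 1.645 or 1.960.

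| Completers per arm | VIF | Effective n | Power, alpha 0.10 | Power, alpha 0.05 |
|---|---|---|---|---|
| 250 | 1.28 | 195.3 | 79.9% | 79.9% |
| 240 | 1.28 | 187.5 | 78.4% | 78.2% |
| 240 | 1.22 | 196.7 | 80.1% | 80.1% |
| 252 | 1.28 | 196.9 | 80.2% | 80.2% |

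**4. VIF at the analysed cluster size**
- If each town loses 20%, 15 × 0.8 = 12 women per town are analysed.
- VIF = 1 + (12 − 1) × 0.02 = 1.22.
- Completers required: 196 × 1.22 = 239.1 per arm.
- Recruits required: 239.1 / 0.8 = 298.9 per arm, against 300 planned.

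On this calculation, which the article does not make, 600 women in 40 towns are enough.

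**5. Keeping 250 instead**
- 313 / 15 = 20.9, so 21 towns per arm, 42 in all.
- 42 × 15 = 630 women; 630 × 0.8 / 2 = 252 completers per arm, a margin of 2.
- If one arm loses one town, it is back to 300 recruits and 240 completers.

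**The case against.** The strongest reply is that 600 is right and only the intermediate 250 is wrong. The section bases the VIF on average cluster size. Using 15 while assuming that 20% of participants are lost charges for clustering among women who will not be analysed. With 12 per town the requirement is 239.1 and the planned 300 recruits per arm cover it. This stands, and it is why the planned size is not in question. It does not rescue the text, which fixes m = 15, a VIF of 1.28 and 250 per group, and reaches 600 from 250 by a step that does not do what it says.

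A reader might infer that the two extra towns are already used up. That follows only if the VIF stays at 1.28, so that 313 per arm are needed. At 1.22, 40 towns suffice and two remain spare.

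A reader might also infer that the abstract contradicts the sample size section. The two can be read together: 600 is the target and 42 the number of towns randomised, and 600/42 = 14.3 per town fits groups of approximately 15. At that spread 11.4 women per town complete, the VIF is 1.209, and 240/1.209 = 198.6 effective women per arm, above 196. What remains is that neither place says whether the two extra towns add women to the 600.

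Finally, the loss in power is small beside the uncertainty in the ICC, which the section says has little published data behind it and which was about zero in the previous trial. At an ICC of zero, 240 completers exceed 196 comfortably. That limits the consequence but does not correct the arithmetic.

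**Conclusion.** The derivation is wrong as written: 250 required, 20% lost and 600 recruited do not fit together. The shortfall against the stated requirement is 10 completers per arm, and the attrition actually allowed for is 16.7%. The shortfall and the attrition limit follow from the article's figures alone. They do not depend on the SD, on how the 90% significance level is read, or on whether 195 or 196 is used.

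The worst case is power of about 78.4% (alpha 0.10) or 78.2% (alpha 0.05) against 80%, and this rests on the back-solved SD and a VIF of 1.28. The tempting conclusion that the trial is underpowered is not supported. If losses are spread evenly so that 12 women per town are analysed, power is about 80% with no extra recruits. If losses fell instead on whole towns, the remaining towns would still hold 15 women and the 1.28 figure would apply. That is the limit of the reassurance, although the section describes its attrition as loss of participants.

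**What to change.** Replace the attrition sentence with one derivation that closes. There are two ways to do so.

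- **Preferred: keep 600 women in 40 towns.** State that 12 of 15 women per town are expected to be analysed, VIF = 1.22, 196 × 1.22 = about 240 completers per arm, and 240 / 0.8 = 300 recruits per arm. The two extra towns are then a true reserve. This costs wording only.
- **Alternative: keep the requirement of 250 at VIF 1.28.** State 250 / 0.8 = 313 recruits per arm, met by 42 towns × 15 = 630 women (252 completers per arm). The two extra towns are then part of the base requirement and should not be called an oversample. This costs 30 more women than the stated 600, in towns already being randomised.

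In either case, give the same target, 600 or 630, in the abstract and in Sample size calculations, and say whether women in the two extra towns count towards it. State the SD used, and use one of 195 or 196 throughout.

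### No stratification or constraint is stated for allocating 42 towns 21:21, although town size and distance are known beforehand; balancing on them is a cheap, modest improvement

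*Protocol article*

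**What the plan says.** The allocation method appears once, at the end of the article's Sample size calculations section, in the sentence about oversampling by two towns: the plan is to "randomise 42 towns using computer generated numbers". The abstract gives the result as "n-21 control towns and n = 21 intervention towns". Neither these sections nor the rest of the article mentions stratification, matching, minimisation or constrained randomisation. The article does not say that the allocation is simple or unrestricted either.

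The Selecting communities section admits "all small rural towns with populations of between 1500–10,000 persons, located within a radius of between 100 km and 400 km" from Melbourne and counts the result: "44 towns will be eligible for randomisation". It gives the reason for the two limits: "these factors are likely to impact on availability and access to health and community services". The same section says of the Shires: "Population statistics and socioeconomic data are readily available for each".

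**The concern.** In a trial that randomises towns, the number of towns governs how well the arms match on town-level features. Recruiting more women per town does not help. The eligibility limits still leave a wide spread: nearly seven-fold in population (10,000/1500 = 6.7) and four-fold in distance (400/100). The plan regards both features as relevant to service access, and both are on file before any town is allocated. Balancing on them would therefore be possible at almost no cost, but only when the sequence is generated. A later analysis plan can adjust for the factors but cannot create balance.

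At stake are some precision in the 12-month weight comparison and the face credibility of the arms as comparable sets of towns.

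**Working it through.** **Inputs from the article.** 21 v 21 towns; target difference 1.0 kg at 12 months; 80% power; 196 women per group before inflation; ICC 0.02; cluster size 15; VIF 1.28; 250 per group after inflation. The significance level is written as 90%, two-sided. I read it as alpha 0.10 and also ran 0.05.

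**Assumption not in the article.** R², the share of between-town variance in weight change explained by town size and distance, is taken as 0.10 to 0.50.

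**Step 1: the plan's own figure.** VIF = 1 + (15 − 1) × 0.02 = 1.28. Then 195 × 1.28 = 249.6 and 196 × 1.28 = 250.9, so the 250 per group is reproduced. No SD is given. Solving back from 196 per group, SD = √(196/2)/(z₁₋α/₂ + z₀.₈). This is 9.90/2.486 = 3.98 kg at alpha 0.10, or 9.90/2.802 = 3.53 kg at alpha 0.05.

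**Step 2: how often the arms would differ if allocation is unrestricted.** Take a two-level factor that splits the 42 towns 21/21, for example at the median population. The number of upper-level towns in one arm is hypergeometric (42, 21, 21).
- P(13-8 or worse) = 0.217
- P(14-7 or worse) = 0.063
- At least one of two independent factors at 13-8 or worse: 1 − (1 − 0.217)² = 0.39

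For a continuous factor, the SD of the arm difference is √(1/21 + 1/21) = 0.31 town-level SD. By simulation (200,000 allocations), the difference exceeds 0.25 SD with probability about 0.43 and 0.5 SD with probability about 0.11.

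**Step 3: what such an imbalance does to the estimate.** Between-town SD = √0.02 × SD = 0.56 kg (alpha 0.10) or 0.50 kg (alpha 0.05). A 0.5 SD imbalance shifts the arm difference by 0.5 × √R² × between-town SD:

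| R² (assumed) | Shift, kg |
|---|---|
| 0.10 | 0.08–0.09 |
| 0.25 | 0.12–0.14 |
| 0.50 | 0.18–0.20 |

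The target is 1.0 kg. The standard error, √(2 × SD² × 1.28/250), is 0.36 to 0.40 kg.

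**Step 4: power gained by balancing and adjusting.** Removing a share R² of the between-town component gives VIF = 1.28 − 15 × 0.02 × R². With 250 analysed per arm:

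| R² (assumed) | VIF | Power |
|---|---|---|
| 0 (as planned) | 1.28 | 79.9% |
| 0.10 | 1.25 | about 81% |
| 0.25 | 1.205 | about 82% |
| 0.50 | 1.13 | 84–85% |

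**Step 5: sensitivity to the ICC.** At ICC = 0, there is no between-town variance to remove and the gain is nil. The article treats the previous trial's ICC of −0.02 as zero, so this end of the range is realistic. It also says there is little published data for rural groups. If the ICC were 0.05 (assumption), VIF would be 1.70 and power 68–69%, rising to 70–71%, 73–74% and 78–79% at R² of 0.10, 0.25 and 0.50.

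**The case against.** The strongest reply is that the defect rests on silence. The phrase about computer-generated numbers says how the sequence is produced, and a stratified or constrained sequence is also computer generated. The article is condensed and has no separate allocation section, so a fuller protocol may describe a restriction. This stands: a reader might infer that the plan specifies unrestricted randomisation, and the article does not say so. The point is limited to what is described.

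A second reply is that the Selecting communities section ties size and distance to service access, not to weight change, and uses them only as eligibility limits that already exclude the extremes. The data called readily available are stated per Shire. This also stands. It is why R² is an assumed range, and why the point is confined to size and distance, which must be known for each town to count the 44 eligible ones. A town-level socioeconomic measure is not shown to be at hand.

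A reader might also infer that imbalance would undermine the primary comparison. The figures do not support that. Chance imbalance under valid randomisation is not bias, a cluster-aware standard error already allows for it, and the shifts in Step 3 are about half a standard error or less. Nor does the article support a claim that comparisons of reach or adoption between arms would suffer. The Community evaluation section describes a process evaluation of implementation and states no such comparison between arms.

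None of these replies points to a restriction in the text or to a real disadvantage in using one.

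**Conclusion.** The point holds as a low-severity design improvement, not as an error. On the description given, nothing keeps the two arms alike on the two town features that the plan singles out. Under unrestricted allocation, a noticeable split on at least one of them has a chance of about 0.39, if the factors are independent and each is divided evenly. The likely benefit of balancing and adjusting is about 1 to 5 power points at ICC 0.02. It is nil at ICC zero and larger if clustering exceeds the plan's guess. These figures rest on the back-solved SD, the plan's own VIF and an assumed R² of 0.10 to 0.50.

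**What to change.** If the towns are not yet allocated, generate the 21:21 allocation within strata of town population and distance from the city (for example, each cut at its median), or by constrained randomisation on both. Constrained randomisation holds the arms at 21:21 even when strata contain odd numbers of towns. Include the same factors in the primary analysis model. State this in one sentence where the allocation is described.

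If the allocation is already done, report whether it was restricted on these factors. If it was not, pre-specify adjustment for town size and distance. That can recover precision but cannot create balance.

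The cost is one changed randomisation program and 2 to 3 degrees of freedom at cluster level, out of about 40 (42 towns less 2 arms). No extra towns, women or staff are needed.
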